## Abstract

**Background:**

Mindfulness has its origins in an Eastern Buddhist tradition that is over 2500 years old and can be defined as a specific form of attention that is non-judgmental, purposeful, and focused on the present moment. It has been well established in cognitive-behavior therapy in the last decades, while it has been investigated in manualized group settings such as mindfulness-based stress reduction and mindfulness-based cognitive therapy. However, there is scarce research evidence on the effects of mindfulness as a treatment element in individual therapy. Consequently, the demand to investigate mindfulness under effectiveness conditions in trainee therapists has been highlighted.

**Methods/Design:**

To fill in this research gap, we designed the PrOMET Study. In our study, we will investigate the effects of brief, audiotape-presented, session-introducing interventions with mindfulness elements conducted by trainee therapists and their patients at the beginning of individual therapy sessions in a prospective, randomized, controlled design under naturalistic conditions with a total of 30 trainee therapists and 150 patients with depression and anxiety disorders in a large outpatient training center. We hypothesize that the primary outcomes of the session-introducing intervention with mindfulness elements will be positive effects on therapeutic alliance (Working Alliance Inventory) and general clinical symptomatology (Brief Symptom Checklist) in contrast to the session-introducing progressive muscle relaxation and treatment-as-usual control conditions. Treatment duration is 25 therapy sessions. Therapeutic alliance will be assessed on a session-to-session basis. Clinical symptomatology will be assessed at baseline, session 5, 15 and 25. We will conduct multilevel modeling to address the nested data structure. The secondary outcome measures include depression, anxiety, interpersonal functioning, mindful awareness, and mindfulness during the sessions.

**Discussion:**

The study results could provide important practical implications because they could inform ideas on how to improve the clinical training of psychotherapists that could be implemented very easily; this is because there is no need for complex infrastructures or additional time concerning these brief session-introducing interventions with mindfulness elements that are directly implemented in the treatment sessions.

**Trial registration:**

From ClinicalTrials.gov, Identifier: NCT02270073 (registered October 6, 2014)

## Background

Mindfulness has its origins in an Eastern Buddhist tradition that is over 2500 years old and can be conceptualized as a specific form of attention that is non-judgmental, purposeful, and focused on the present moment (Cigolla and Brown 2011; Heidenreich and Michalak 2003). Currently, it is well established in cognitive-behavior therapy (CBT), with mindfulness-based stress reduction (MBSR; (Kabat-Zinn 1990; Grossman et al. 2004)) as its most prominent application. Usually, mindfulness interventions have been investigated in a structured, manualized group setting (Bohlmeijer et al. 2010). However, an increasing demand to further investigate the effects of mindfulness practiced together by patients and therapists in individual therapy under naturalistic conditions has been highlighted to address external validity issues (e.g. (Ryan et al. 2012; Bruce et al. 2010)).

### Therapist mindfulness practice and therapeutic alliance

Concerning the therapist’s perspective, it has been highlighted that qualities such as empathy, understanding, warmth, genuineness, and acceptance have been found to be important for developing a positive therapeutic alliance and for predicting therapeutic outcome (Lambert and Barley 2002; Orlinsky et al. 2004). Furthermore, they have been found to be positively related to mindfulness practice (Cigolla and Brown 2011; Horst et al. 2013). Consequently, a two-stage model concerning the association between mindfulness and the activation of a therapeutic alliance has been hypothesized: Mindfulness practice improves self-acceptance and self-compassion as preconditions for the further development of empathy and acceptance towards patients (Bruce et al. 2010; Kristeller and Johnson 2005; Siegel 2007). Consequently, the strength of the therapeutic alliance might be enhanced (Horst et al. 2013).

### Patient mindfulness practice and explanation of clinical improvements

Concerning the patient’s perspective, it has been hypothesized that mindfulness practice leads to a better sense of self-acceptance, better emotion regulation, increased body awareness, and an improvement of interpersonal relationships (Bruce et al. 2010; Hölzel et al. 2011). This in turn may explain the associations between patients’ mindfulness practice and improvements in therapeutic alliance, general wellbeing, emotional clarity, self-esteem, and life satisfaction that have been identified by several studies (Brown and Ryan 2003; Shapiro et al. 2008; Baer et al. 2004; Dunn et al. 2013).

### Mindfulness in effectiveness research in trainee therapists

In the context of investigating the mutual mindfulness experiences of patients and therapists, it has been specifically highlighted that brief, in-session mindfulness interventions should be investigated in trainee therapists (Dunn et al. 2013; Grepmair et al. 2007), as this would elucidate opportunities to improve clinical training (Ryan et al. 2012).

Nevertheless, only a few studies have been conducted addressing these limitations: In an inpatient study, the patients of therapists in training who received a 2-month Zen-meditation workshop program showed a stronger symptom reduction than a control group did (Grepmair et al. 2007). Another study demonstrated that trainee therapists’ dispositional mindfulness did not directly predict therapeutic outcome but was associated with improvements in the interpersonal functioning of the patient and the therapeutic alliance (Ryan et al. 2012). Additionally, an analysis of interview transcripts in a qualitative study demonstrated that the shared experience of mindfulness of both patient and trainee therapist led to improvements in therapeutic alliance and was helpful with transitions from everyday activity to therapy sessions (Horst et al. 2013). Furthermore, a study in which trainee therapists conducted a 5-min mindfulness-centering exercise before therapy sessions resulted in therapists perceiving themselves as being more present and in patients perceiving therapeutic alliances as being stronger and therapy as being more effective compared to a control group (Dunn et al. 2013). This cross-sectionally designed study highlights that it seems to be auspicious to implement brief mindfulness interventions in a longitudinally designed, randomized controlled trial of therapists in training. However, there is also a study that demonstrated a negative association of trainee therapists’ self-reports of dispositional levels of mindfulness and therapeutic outcomes (Stanley et al. 2006).

### Mindfulness studies with active control groups

In spite of this preliminary evidence of positive effects of mindfulness on therapeutic alliance, little is known about the specific mechanisms of mindfulness in psychotherapy (Coffey et al. 2010). Furthermore, only a few studies have compared mindfulness interventions with an active control group, and most of the investigations that did were conducted with non-clinical samples. Most studies applied progressive muscle relaxation (PMR) as an active control group and demonstrated the beneficial effects of mindfulness (e.g. (Feldman et al. 2010; Semple 2010)). Hence, randomized controlled trials with a focus on associations of mindfulness with therapeutic alliance from both the patient and therapist perspectives are needed (Ryan et al. 2012; Bruce et al. 2010; Horst et al. 2013). This research should be conducted under naturalistic conditions, because effectiveness studies are generally demanded by leading psychotherapy researchers to address issues of external validity (Orlinsky et al. 2004; Lambert 2013; Norcross and Lambert 2011; Lutz 2003; Flückiger et al. 2012).

### Objectives

The main purpose of this study is to identify whether exercises with mindfulness elements carried out at the beginning of individual therapy sessions help to improve the therapeutic process under effectiveness conditions. Consequently, we designed a study to analyze the effects of a 5-min session-introducing intervention with mindfulness elements (SIIME) conducted together by trainee therapists and their patients in a randomized, controlled, longitudinal design under naturalistic conditions with PMR as the active control group.

More specifically, we will examine the effects of SIIME practiced by both outpatients and CBT trainee therapists at the beginning of the 25 therapy sessions (brief-term CBT of the German healthcare system) on (a) therapeutic alliance measured on a session-to-session basis and (b) on clinical outcomes assessed every 10 sessions. Thus, before the start of therapeutic treatment, patients are randomized into a treatment-as-usual + mindfulness intervention group (TAU + M) practicing SIIME, a TAU + PMR-control group practicing a session-introducing short form of PMR, or a TAU control group without standardized session-introducing intervention. Before the start of the intervention study, all therapists will participate in a 6-week workshop-based mindfulness and PMR program. We will investigate the following hypotheses:We hypothesize that both patients and therapists of the TAU + M will experience higher levels of therapeutic alliance compared to the TAU + PMR and TAU.We hypothesize that in the TAU + M, there will be stronger reductions in clinical symptomatology of patients compared to the TAU + PMR and TAU.

The results of the planned study are important in three ways. First, they will complement earlier preliminary evidence on the effects of mindfulness on therapeutic alliance and clinical improvements by addressing the above-mentioned research gaps in effectiveness research. Second, they will more specifically elucidate the potential beneficial effects of brief SIIME as a tool to introduce therapy sessions. Third, they could provide important practical implications: The results could deliver ideas about how to improve the training of psychotherapists in outpatient training centers. If they are replicated in other studies, positive results could lead to important developments in modifications of psychotherapy training that could be implemented very easily, as there is no need for complex infrastructures or additional time concerning these SIIME that are directly implemented in the treatment sessions.

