### Sample and ethics

A total of 30 trainee therapists and 150 patients will be recruited at the CPP. Enlisting as a trainee in the clinic is preceded by a rigorous assessment that evaluates the potential trainee’s personal suitability for becoming a CBT therapist.

The general inclusion criterion for patients is a primary depressive- or anxiety-disorder diagnosis in the Structured Clinical Interview according to the DSM-5 criteria (Falkai et al. 2014). We chose these two disorder groups because from patients being treated at German university therapy-training centers; approximately 40 % suffer from a primary major depression, and approximately 30 % suffer from a primary anxiety disorder (e.g. (Nelson and Hiller 2013)). Hence, our results will be of importance to a majority of outpatient diagnostic groups.

The general exclusion criteria for patients will be as follows: (1) an age below 18 or above 65 years, (2) insufficient German language skills, (3) those suffering from a psychotic disorder, (4) current suicidal risk. Comorbidities with disorders not on the exclusion list are generally not considered as limitations to entering the study, as long as depression and anxiety disorders are of primary concern.

Power analyses with G*Power (Faul et al. 2007) for the detection of small effects (Cohen’s *f* = 0.12) for the interaction between time (pre, mid-5, mid-15, post) and treatment condition (TAU-M versus TAU-PMR versus TAU) (ANOVA repeated measures, within-between-interaction, α = 0.05, power = 0.80, number of groups = 3, number of measurements = 4, pre-post correlation *r* = 0.05, nonsphericity correction = 1) along with practical clinical considerations (Flückiger 2014) resulted in a sample size of 123 patients. Taking potential dropouts into account, a total sample of 150 patients will be assigned to one of the three groups by a stratified randomization process. Patients will be stratified into one of two categories: one group with the main diagnosis of major depression and the other group with the main diagnosis of an anxiety disorder.

Voluntary participation and written, informed consent are necessary conditions for participation in the study. The local ethics committee (Ethikkommission der Fakultät für Verhaltens- und Empirische Kulturwissenschaften der Universität Heidelberg) approved the study protocol in accordance with the Helsinki Declaration.

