### Statistical analysis

We will compare baseline descriptive statistics between the three study arms with *χ*^2^-tests (for categorical variables) and with ANOVA / t-tests (for continuous variables).

In line with the recommendations of Baldwin, Imel, Braithwaite, and Atkins (Baldwin et al. 2014), we will apply a multilevel modeling approach to address the nested data structure (sessions at level 1 are nested within patients at level 2, which are nested within therapists at level 3): Thereby, we will treat time as a within-subject factor and treatment condition as a between-subject factor. We will analyze main effects, that is, differences in intercepts of TAU + M versus TAU + PMR versus TAU concerning process and outcome variables, and interactive effects, that is, differences in slopes of TAU + M versus TAU + PMR versus TAU concerning process and outcome variables (Raudenbush and Bryk 2002). Our statistical hypothesis implies that the intercept is significantly higher in the TAU + M than in the TAU + PMR and the TAU concerning both the process and outcome variables. Additionally, it implies that the slope increases significantly stronger in the TAU + M than in the TAU + PMR and the TAU concerning both the process and outcome variables. We will conduct analyses on the intention-to-treat sample as well as on the completer sample. Furthermore, patients’ and therapists’ pre-treatment characteristics will be investigated as outcome predictors at levels 2 and 3 to control for differential effects on outcome in the three treatment arms.

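### The statistical hypothesis adds an intercept difference for the symptom outcomes, with no time origin given; counted from Pre, that contrast is a pre-treatment comparison and says nothing about symptom reduction

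*Protocol article*

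**What the plan says.** The Objectives section states two hypotheses of different kinds. The first concerns the level of therapeutic alliance. The second concerns change: "in the TAU + M, there will be stronger reductions in clinical symptomatology of patients compared to the TAU + PMR and TAU". Patients are randomised before treatment begins (same section).

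The symptom outcome has a wave before any exercise takes place: "Clinical symptomatology will be assessed at baseline, session 5, 15 and 25". Table 1 shows the same Pre wave for BDI-II, BAI, IIP, GAF and the patient KIMS. Alliance (WAI-SR) is rated at sessions 1 to 25 and has no Pre wave.

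The sample size in Sample and ethics is calculated "for the interaction between time (pre, mid-5, mid-15, post) and treatment condition", and for no other effect.

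The Statistical analysis section then treats both kinds of variable alike. It defines the main effects as "differences in intercepts of TAU + M versus TAU + PMR versus TAU concerning process and outcome variables". It goes on to say that the "intercept is significantly higher in the TAU + M than in the TAU + PMR and the TAU concerning both the process and outcome variables", and adds that "the slope increases significantly stronger in the TAU + M than in the TAU + PMR and the TAU". It does not say at which wave time equals zero.

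**The concern.** In a growth model the intercept is the expected value where time equals zero, so an intercept difference between arms means nothing until that point is fixed. For a variable with a Pre wave, and with time counted from the first wave, it is the arm difference before treatment. Randomisation makes that zero in expectation, and a significant result can only be chance imbalance.

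The GSI is one of two primary outcomes, and this sentence describes what the authors expect to see if their hypothesis is true. Two misuses are open:

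- If intercept and slope must both be significant, a real treatment effect could fail to be confirmed because the arms were comparable at baseline.
- If an intercept difference counts by itself as a treatment main effect, a baseline imbalance could be reported as a benefit.

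This is separate from the printed direction. For symptom scores a higher intercept and a rising slope point the wrong way, but changing higher to lower would leave the same pre-treatment comparison.

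**Working it through.** **Inputs from the protocol article.** Waves at sessions 0 (Pre), 5, 15 and 25; 150 patients in three arms, so 150/3 = 50 per arm; f = 0.12, α = 0.05, power 0.80, 3 groups, 4 measurements, correlation 0.05; stated sample size 123.

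**Assumptions.** Unit SD at every wave; equal correlation r between waves; arm difference zero at Pre and growing linearly to 0.6 SD at session 25; one control comparison; the predicted direction taken as the beneficial one; no dropout; no therapist clustering; two-sided 5% tests, normal approximation.

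**The plan's own figure.** For the interaction, λ = f²·N·m/(1 − r) with 6 and 3(N − 3) degrees of freedom. With the printed r = 0.05 this needs N = 227, and power at 123 is 0.49. With r = 0.5 it needs 121, or 123 for equal arms. So 123 is reproduced only with r = 0.5, which is used as the central value below. The printed 0.05 is a separate matter.

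**Slope contrast.** Mean time = (0 + 5 + 15 + 25)/4 = 11.25. Sum of squares about it = 126.5625 + 39.0625 + 14.0625 + 189.0625 = 368.75. For two arms of 50 the variance factor is 2/50 = 0.04.

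SE of the slope difference, scaled to 25 sessions = 25·√(0.04 × 0.5/368.75) = 0.184. Then z = 0.6/0.184 = 3.26, and power = Φ(3.26 − 1.96) = 0.90.

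**Intercept contrast at origin c.** Its expectation is 0.6·c/25. Its variance is 0.04·[(1 + 3r)/4 + (1 − r)(11.25 − c)²/368.75].

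- c = 0 (Pre): expectation 0. SE = √(0.04 × (0.625 + 0.1716)) = 0.179. Rejection in the predicted direction is 2.5% for any effect size.
- c = 11.25 (centred): expectation 0.6 × 0.45 = 0.27. SE = √(0.04 × 0.625) = 0.158. z = 1.71, power 0.40.
- c = 25 (end of treatment): expectation 0.6. SE = √(0.04 × (0.625 + 0.2564)) = 0.188. z = 3.20, power 0.89.

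**Both contrasts significant** (bivariate normal; at r = 0.5 the correlation of the two estimates is −0.46, 0 and 0.54 for the three origins):

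| r | Slope alone | Both, origin Pre | Both, centred | Both, origin session 25 |
|---|---|---|---|---|
| 0.05 | 0.66 | 0.001 | 0.47 | 0.65 |
| 0.3 | 0.79 | 0.006 | 0.39 | 0.76 |
| 0.5 | 0.90 | 0.015 | 0.36 | 0.83 |
| 0.7 | 0.99 | 0.023 | 0.33 | 0.87 |

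**Simulation check** (50 per arm, r = 0.5, 4,000 replicates, two-sided). For true final effects of 0.3, 0.5 and 0.8 SD, the intercept test with origin at Pre rejects in 0.050, 0.051 and 0.052 of trials, and the slope test in 0.36, 0.76 and 0.99. At 0.5 SD the intercept test rejects in 0.30 when centred and 0.75 with the origin at session 25.

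**No effect at all.** The contrasts of TAU + M with the two controls share an arm, so they correlate at 0.5. The chance that at least one intercept contrast is significant is about 9%.

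**The case against.** The strongest reply is that the article never places the origin at Pre. It writes "We will analyze main effects, that is, differences in intercepts of TAU + M versus TAU + PMR versus TAU", which suggests that the intercept is meant to carry a treatment effect. That would fit a centred or end-of-treatment origin better. Time coding is also a detail that a condensed article may leave to the analysis plan. This stands in part: the zero-expectation result depends on the coding, and with the origin at session 25 the intercept test is about as powerful as the slope test. But nothing in the article points to that origin, Pre is the first listed level of the time factor, and centring still mixes in an untreated wave. The point is also not a missing detail: the article positively extends the intercept hypothesis to outcome variables.

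Second, the slope contrast is specified for outcome variables and is the effect the trial is sized for. This stands fully. A reader might infer that the plan cannot test its second hypothesis. The documents do not support that.

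Third, the article prints no rule that both contrasts must be significant, or that the intercept alone suffices. It says what the hypothesis implies, and adds the slope. A reader might infer that power falls from 90% to 1.5%. That needs the Pre origin and the joint requirement together, and neither is stated. Likewise, 9% is the ordinary false-positive chance of two correlated 5% tests. It does harm only if a Pre difference is reported as a treatment effect.

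**Conclusion.** The concern holds in a limited form. The Statistical analysis section extends an intercept hypothesis suited to alliance to outcomes whose hypothesis concerns change, and leaves the time origin open. From Pre, the contrast carries no information on the treatment; centred, it carries 0.45 of a linear final effect; only at or near session 25 is it a useful treatment contrast. The second hypothesis remains tested by the slope contrast. The fault is the added criterion and the two misuses it allows.

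The zero expectation at Pre follows from randomisation alone. The 0.45 needs only linearity and equal weighting of the four waves. The power figures are illustrative. They rest on an assumed correlation, a 0.6 SD effect, 50 per arm, no dropout and no therapist clustering; the joint figures also assume that both tests are required.

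**What to change.** Amend the Statistical analysis section as follows:

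1. Limit the intercept hypothesis to therapeutic alliance, which has no Pre wave.
2. For the GSI and the other patient variables with a Pre wave (BDI-II, BAI, IIP, GAF, patient KIMS), decide the hypothesis on the condition difference in change from Pre. This can be the time-by-condition contrast or the model-based difference at session 25. Choose one and state the time origin.
3. State that an arm difference at Pre is not interpreted as a treatment effect.

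This takes a sentence or two and needs no further data or patients. It brings the section into line with the Objectives and the sample size calculation. What is given up is the option of reporting a baseline difference as a main effect. The direction wording for symptom scores can be corrected in the same edit.

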## Method

### Standard procedures at the Center for Psychological Psychotherapy

The Center for Psychological Psychotherapy (CPP) is a large university outpatient training center for CBT at the University of Heidelberg. Approximately 1000 patients per year with different types of psychiatric disorders (about two-thirds suffering from anxiety and depression) are treated there by approximately 100 trainee therapists. The CPP has 14 rooms for providing psychotherapy. All rooms offer the opportunity to videotape sessions and to listen to audiotapes.

The training of therapists at the CPP follows the standard procedures of CBT formation in Germany. Specifically, all trainees receive a minimum of 600 h of theory, 150 h of supervision, and 120 h of self-experience, and they perform 600 h of outpatient therapy. Furthermore, before beginning with individual outpatient therapy, they perform 18 months of internships in psychiatric and psychosomatic hospitals. All outpatient therapy sessions are supervised by accredited experts. Outpatient sessions begin after a six-session diagnostic stage and are not based primarily on specific CBT treatment manuals but rather on individual case formulations as developed by trainees in collaboration with their supervisors to guarantee the optimal adaptation of therapeutic interventions for the individual needs of patients. Outcome assessments at the baseline, at every tenth session during treatment, at the end of therapy, and at a 12-month follow-up are standard procedure at the CPP.

